### Aims and outcome measures

2.7

The primary aim of this study is to assess the feasibility of recording gut-related interoceptive EEG responses in patients with disorders of consciousness under standardized stimulation conditions.

The primary outcomes are predefined electrophysiological measures, including:(1) ERP component amplitude and latency (N1, P2, P3) time-locked to rectal distension, and.(2) Event-related spectral perturbation (ERSP) in the theta (4–7 Hz) and alpha (8–12 Hz) frequency bands.

Secondary exploratory outcomes include group-level comparisons of these electrophysiological measures among UWS, MCS, and healthy control participants, as well as exploratory associations between EEG markers and CRS-R total scores and subscale scores.

All outcomes are exploratory and group-level in nature. This study is not designed to support individual-level diagnostic classification or clinical decision-making, but rather to assess feasibility and to provide preliminary effect size estimates that may inform the design of future hypothesis-driven and validation studies.

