# Detection of residual consciousness using EEG indicators related to rectal perception: protocol for a diagnostic accuracy study

**DOI:** 10.3389/fneur.2026.1802303

**Published:** 2026-05-20

**Keywords:** diagnosis, disorders of consciousness, gut-brain axes, interoception, rectum

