### Study design and setting

2.1

This study is designed as a prospective, observational, exploratory study. Its primary objective is to evaluate the feasibility, signal characteristics, and descriptive group-level electrophysiological patterns associated with gut-related interoceptive processing in patients with DoC, rather than to establish diagnostic accuracy or individual-level classification. The study is conducted in the General Department of Hyperbaric Oxygen at the Second People’s Hospital of Hefei (Hefei, China).

The center has established a specialized system covering diagnostic confirmation and comprehensive management, which includes standardized diagnostic workflows, a bedside electroencephalography (EEG) system (iRecorder W32), and a multidisciplinary clinical research team proficient in interoceptive testing and DoC research. Additionally, the controllable rapid inflation-deflation rectal stimulation device was independently developed by the research team (Figure 1). These resources ensure protocol adherence, data uniformity, and participant safety throughout the entire study period. The study will be reported in accordance with STARD-informed principles where applicable, with an emphasis on transparent reporting of study design, participant flow, and analytical procedures.

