From a public health perspective, the potential relevance of this work extends beyond individual-level assessment. Advanced neuroimaging techniques such as fMRI and FDG-PET, while informative, are costly, resource-intensive, and often inaccessible in low and middle-income settings. EEG-based paradigms that can be implemented at the bedside offer a more scalable and equitable approach to DoC research. If feasibility and systematically characterizable neural responses are demonstrated, this line of research may contribute to the development of accessible assessment strategies aligned with public health priorities of feasibility, equity, and responsible resource utilization.

Several limitations of the present protocol should be acknowledged. The relatively small sample size and single-center design limit generalizability and preclude conclusions regarding diagnostic performance or individual-level classification. Moreover, interoceptive processing may be influenced by factors such as medication exposure, autonomic dysfunction, and gastrointestinal comorbidities, which will require systematic control in future studies. In addition, this protocol is not designed to establish causal relationships between interoceptive neural responses and conscious awareness. These considerations underscore the exploratory nature of the present work and highlight the need for subsequent multicenter and longitudinal investigations with larger cohorts and predefined validation frameworks.

Importantly, this protocol is intended to serve as an initial methodological step within a staged translational research pathway rather than as a diagnostic validation study. The primary objective is to establish feasibility, tolerability, and signal-level characteristics of gut-related interoceptive EEG responses under standardized bedside conditions, thereby generating essential methodological parameters and effect size estimates to guide subsequent multicenter and hypothesis-driven investigations.

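### The primary aim is feasibility, but every primary outcome is an ERP or ERSP value, so no listed outcome can support or count against feasibility or tolerability

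*Protocol article*

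**What the plan says.** The protocol article describes its main purpose in three places, not identically.

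- Section 2.1: "Its primary objective is to evaluate the feasibility, signal characteristics, and descriptive group-level electrophysiological patterns associated with gut-related interoceptive processing", and this "rather than to establish diagnostic accuracy or individual-level classification".
- Section 2.7: "The primary aim of this study is to assess the feasibility of recording gut-related interoceptive EEG responses in patients with disorders of consciousness".
- Section 3 (Discussion): "The primary objective is to establish feasibility, tolerability, and signal-level characteristics of gut-related interoceptive EEG responses under standardized bedside conditions".

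Directly after the aim, Section 2.7 states "The primary outcomes are predefined electrophysiological measures". It lists amplitude and latency for N1, P2 and P3, and ERSP in the theta and alpha bands. Comparisons between UWS, MCS and healthy controls, and associations with CRS-R scores, are secondary and exploratory.

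Section 2.6 specifies a one-way ANOVA per electrophysiological outcome with Tukey post hoc comparisons. Section 2.5 derives the sample size from a two-group t-test on pilot ERP amplitude, but says the size is meant to serve feasibility assessment and effect size estimation.

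The title calls the article a "protocol for a diagnostic accuracy study".

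**The concern.** A primary outcome should measure the primary aim. Here the aim and the outcomes stand next to each other in Section 2.7 and do not match. No primary or secondary outcome is a completion rate, a rate of usable recordings, a rate of early stopping or a criterion for the presence of a response. No result is named that would count as feasible or as not feasible.

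Followed as written, the plan delivers group means, F-tests and effect sizes. A conclusion that the paradigm is feasible would then rest on no prespecified measure, and no listed result could contradict it. This matters because the Discussion wants the study to supply methodological parameters for later multicentre work, and those studies will need to know how often the procedure can be completed and yields analysable EEG.

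**Working it through.** **1. Count the primary outcomes (Section 2.7).** 3 components × 2 measures = 6 ERP values; 2 bands = 2 ERSP values; 6 + 2 = 8. All are electrophysiological.

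**2. Set each stated objective against the listed outcomes.**

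| Objective | Where stated | Listed outcome that measures it |
|---|---|---|
| Feasibility | 2.1, 2.7, 3 | none |
| Tolerability | 3 only | none |
| Signal characteristics | 2.1, 3 | the eight ERP/ERSP values |
| Group-level patterns | 2.1 | group comparisons (secondary) |

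**3. Ask whether the eight values could stand in for feasibility.** Section 2.6 takes the mean amplitude and the peak latency in fixed windows. Both can be computed for any usable epoch average, including one with no evoked response. Neither exists for a patient who could not be recorded. So they carry no information on how often recording succeeded, and without a test against baseline they do not establish that a response was present. The ANOVA compares groups with each other; a null result fits equally well with a response in every group and a response in none.

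**4. Reproduce the plan's own figure (Section 2.5).** Inputs: d = 1.13, two-sided α = 0.05, power 80%.

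- Normal approximation: n = 2(1.960 + 0.842)² / 1.13² = 2 × 7.85 / 1.277 = 12.3, so 13 per group, as stated.
- Exact noncentral t: n = 13.33, so 14. Power is 78.9% at 13, 82.1% at 14 and 84.8% at the target of 15.

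The one-participant difference is immaterial here. What matters is the target of the calculation: a pairwise difference in ERP amplitude, which Section 2.7 ranks as secondary, and not any feasibility quantity.

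**5. What the planned size would give for a feasibility proportion.** The target is 15 per group, so 30 DoC patients. For x successes among n, the exact (Clopper–Pearson) 95% limits are: lower = Beta⁻¹(0.025; x, n − x + 1), upper = Beta⁻¹(0.975; x + 1, n − x). The article gives no expected rate, so the values of x are assumptions that span a plausible range.

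| Assumed result | Proportion | Exact 95% interval |
|---|---|---|
| 30/30 | 100% | 88–100% |
| 27/30 | 90% | 73–98% |
| 24/30 | 80% | 61–92% |
| 15/15 | 100% | 78–100% |
| 13/15 | 87% | 60–98% |
| 12/15 | 80% | 52–96% |

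For tolerability, if no event is seen, the one-sided 95% upper bound is 1 − 0.05^(1/n): 9.5% for n = 30 and 18.1% for n = 15.

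**6. Title.** It names diagnostic accuracy. Sections 2.1, 2.5, 2.7 and 3 each say that the study is not designed for that, and no accuracy measure is planned.

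**The case against.** **The article is condensed, and an analysis plan may hold the detail.** This would excuse a missing definition or test. It does not excuse the mismatch, because Section 2.7 itself fixes the primary outcomes, and an analysis plan should implement them, not replace them.

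**The study is exploratory.** That excuses the absence of confirmatory testing. It does not excuse the absence of any measure of the stated aim.

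**The ERP/ERSP values are informative.** This stands in part. Sections 2.1 and 3 include signal characteristics in the primary objective, and the eight values address these directly. ERSP normalised to baseline would also centre near zero at group level if there were no response, so it bears on presence; peak latency does not. No test or criterion is attached to either.

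**Counts will be reported anyway.** This also stands in part. Section 2.1 promises transparent reporting of participant flow, Sections 2.3 and 2.4.4 provide for monitoring and discontinuation, and Section 2.4.3 for data quality control. The information would largely exist. What is missing is its status as an outcome, with a denominator, an interval and a criterion.

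Three stronger readings are tempting but not supported:

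- That patients stopped for discomfort will disappear as dropout. Section 2.5 only allows for data loss or dropout in the sample size; no rule for stopped sessions is given either way.
- That eight ANOVAs at 0.05 make the primary result unreliable. If they were independent, 1 − 0.95⁸ = 34% is the chance of at least one false group difference. But those comparisons are declared secondary and exploratory, and the figure says nothing about feasibility.
- That tolerability is a primary aim throughout. It appears as an objective only in the Discussion.

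**Conclusion.** The concern holds for feasibility and tolerability. Section 2.7 names feasibility of recording as the primary aim, and none of its eight primary outcomes, nor any secondary one, measures it. The same is true of tolerability, which the Discussion adds.

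A reader might go further and infer that the study cannot answer its primary question at all. The documents do not support that, since signal characteristics belong to the objective in Sections 2.1 and 3 and are covered.

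The flaw lies in the definition and ranking of outcomes, not in the data to be collected or the number of patients. At 30 patients a feasibility proportion could be estimated with a lower 95% limit between about 61% and 88% for assumed observed rates of 80% to 100%; at 15 per group the limits are wider. These figures assume that all targeted participants start the procedure.

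The title is a separate, plain contradiction of the text, and editorial in its consequences. Whether the registry entry shares the wording cannot be judged from the article.

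**What to change.** 1. **Primary outcomes.** Report the following per group and for all DoC patients together, with exact 95% intervals and everyone who starts the procedure as denominator: the proportion completing the 35-trial sequence; the proportion with a preset minimum number of artifact-free epochs; and the proportion stopped early, with the reason.
2. **Presence of a response.** Add a group-level test against the pre-stimulus baseline. Surrogate epochs from the inter-stimulus EEG are an alternative, but they must exclude inflation and deflation; deflation is passive and its duration is not stated in Section 2.4.2, so the excluded interval has to be defined. Individual responder labels are better avoided, because Sections 2.1 and 2.7 confine the study to group-level statements.
3. **Criterion.** State in advance what result would count as feasible.
4. **Ranking.** Keep the ERP/ERSP values as signal-characterisation outcomes below the feasibility measures. Section 2.5 does not say which component the pilot amplitude refers to, so if one key measure is wanted it must be named.
5. **Sample size.** Add a sentence on the precision that 15 per group and 30 patients give for the feasibility proportions.
6. **Wording.** State the primary objective identically in Sections 2.1, 2.7 and 3, and remove the diagnostic accuracy label from the title.

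The cost is a revised outcome list and light extra analysis. It needs no additional participants and no new recordings, provided that completion and reasons for stopping are noted for each session.

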### Patient and public involvement

2.8

Patients and members of the public were not involved in the design, conduct, reporting, or dissemination of this study.

### Ethics

2.9

This study protocol has been registered on ClinicalTrials.gov (NCT07208942) and approved by the Ethics Committee of the Second People’s Hospital of Hefei (Approval No: 2024-Research-170). The study will be conducted in strict adherence to the Declaration of Helsinki and local regulatory requirements to ensure participant safety and ethical integrity.

Prior to initiating any study procedures, written informed consent will be obtained from all participants (or their legal guardians, for patients with DoC). To ensure comprehension, consent information will be provided in both written (simplified Chinese) and oral formats, with opportunities for questions to be addressed by the study team. For DoC patients unable to provide consent, approval will be sought from an immediate family member or legal representative—who will receive a detailed explanation of the study’s purpose, procedures, risks and benefits.

To protect participant privacy, all data (case report forms, CRS-R assessments, EEG recordings, rectal manometry results) will be labeled only with unique participant codes (no names, medical record numbers, or other). Physical documents will be stored in locked filing cabinets in a restricted-access room; electronic data will be saved on password-protected, study-specific computers with access limited to authorized personnel (co-investigators, data managers). Personally identifiable information will not be shared with third parties, including commercial entities or non-study clinicians. Research-related personal data will be retained for 5 years following the publication of final results and then securely destroyed in compliance with institutional policies and China’s Personal Information Protection Law.

## Discussion

3

The present study protocol addresses a persistent and clinically consequential limitation in current approaches to the assessment of disorders of consciousness (DoC): the lack of objective methods capable of probing dimensions of consciousness that extend beyond overt behavioral responsiveness. Despite substantial advances in neurocritical care, routine diagnostic practice continues to rely predominantly on behavior-based assessments, which are inherently vulnerable to motor impairment, fluctuating arousal, and cognitive–motor dissociation. These limitations have been widely recognized and have important implications for diagnostic classification, prognostication, and care planning.

From a theoretical standpoint, contemporary models of consciousness emphasize that conscious experience is not defined solely by externally directed awareness, but also by internal self-related processes, including interoceptive perception. Interoception represents a core neurobiological substrate of self-awareness and is supported by distributed neural systems involving the insular cortex, anterior cingulate cortex, and brainstem arousal networks. However, this dimension remains largely absent from existing diagnostic paradigms for DoC. By proposing an EEG-based gut-related interoceptive assessment, the present protocol aims to explore the feasibility of capturing neural responses to internal bodily signals in DoC patients, thereby providing a complementary perspective to externally driven evaluation frameworks.

Methodologically, this study is explicitly designed as an exploratory and feasibility-focused investigation rather than a confirmatory diagnostic accuracy trial. The use of standardized rectal balloon distension combined with synchronized EEG acquisition enables controlled activation of the gut–brain axis while remaining compatible with bedside clinical settings. Compared with cardiac-based interoceptive measures, gut-related interoceptive signals may be less susceptible to transient autonomic fluctuations and external noise, which could represent a potential methodological advantage in severely brain-injured populations. Importantly, the present protocol prioritizes signal characterization, group-level pattern description, and preliminary effect size estimation, with the primary goal of informing the design of future hypothesis-driven and validation studies.

From a public health perspective, the potential relevance of this work extends beyond individual-level assessment. Advanced neuroimaging techniques such as fMRI and FDG-PET, while informative, are costly, resource-intensive, and often inaccessible in low and middle-income settings. EEG-based paradigms that can be implemented at the bedside offer a more scalable and equitable approach to DoC research. If feasibility and systematically characterizable neural responses are demonstrated, this line of research may contribute to the development of accessible assessment strategies aligned with public health priorities of feasibility, equity, and responsible resource utilization.

Several limitations of the present protocol should be acknowledged. The relatively small sample size and single-center design limit generalizability and preclude conclusions regarding diagnostic performance or individual-level classification. Moreover, interoceptive processing may be influenced by factors such as medication exposure, autonomic dysfunction, and gastrointestinal comorbidities, which will require systematic control in future studies. In addition, this protocol is not designed to establish causal relationships between interoceptive neural responses and conscious awareness. These considerations underscore the exploratory nature of the present work and highlight the need for subsequent multicenter and longitudinal investigations with larger cohorts and predefined validation frameworks.

Importantly, this protocol is intended to serve as an initial methodological step within a staged translational research pathway rather than as a diagnostic validation study. The primary objective is to establish feasibility, tolerability, and signal-level characteristics of gut-related interoceptive EEG responses under standardized bedside conditions, thereby generating essential methodological parameters and effect size estimates to guide subsequent multicenter and hypothesis-driven investigations.

### Prospects for scalable and equitable diagnostics

3.1

Building on the outcomes of this protocol, future investigations are expected to progress toward multicenter studies with larger and more heterogeneous cohorts, in which interoceptive EEG markers can be systematically evaluated for their added value in patient stratification and diagnostic enrichment. Rather than serving as a standalone diagnostic tool, gut-related interoceptive EEG paradigms may ultimately function as a complementary modality alongside behavioral assessment and existing neurophysiological measures, particularly for probing neural responses potentially related to internal aspects of awareness in patients with limited or absent motor output.

From a public health perspective, the long-term translational relevance of this approach lies in its potential scalability and accessibility. As a low-cost, portable, and bedside-compatible technique, EEG-based interoceptive assessment may be particularly well suited for implementation in resource-limited settings, where advanced neuroimaging modalities are often unavailable. If validated in future studies, such paradigms could contribute to more equitable and standardized evaluation pathways for disorders of consciousness, supporting responsible allocation of rehabilitative resources and improving population-level care strategies.

### Potential risks, burdens, and benefits

3.2

The proposed protocol involves controlled rectal balloon distension combined with EEG recording, which warrants careful consideration of potential risks, participant burden, and anticipated benefits. Rectal distension may induce transient discomfort or mild autonomic responses, such as changes in heart rate or blood pressure. However, the stimulation parameters employed are comparable to procedures routinely used in clinical bowel care for patients with prolonged disorders of consciousness. All procedures will be conducted under continuous bedside monitoring by trained clinical personnel, with predefined stopping criteria and immediate access to medical support to ensure participant safety.

Overall participant burden is considered low. EEG recording is non-invasive and widely used in routine neurological practice, and the rectal stimulation protocol is time-limited and integrated into standard nursing workflows. Importantly, participation in this study will not alter routine clinical management or influence diagnostic or therapeutic decision-making for enrolled patients.

While no direct clinical benefit to individual participants can be expected, the potential scientific and societal benefits are meaningful. By systematically exploring an underexamined dimension of consciousness, this study may provide foundational evidence to inform future research aimed at developing more comprehensive, accessible, and theoretically grounded assessment approaches for DoC. In the longer term and at the population level, such advances may support improved research stratification, more informed prognostic discussions, and the responsible allocation of healthcare resources, in line with public health priorities.
